#### Spatial pattern separation memory test

The pattern separation memory test [38] is a computer-based assessment designed to evaluate episodic memory, utilizing a collection of 140 colour images depicting commonplace neutral objects against a white background. This cognitive task consists of two phases. The first phase is the encoding phase. During this initial stage, participants are presented with each image and tasked with categorizing it as either “nice” or “not nice” by pressing designated buttons. Each image is displayed for 2 s, with a 0.5-s inter-stimulus interval. Immediately following the encoding phase, participants are informed of a surprise recognition memory test, which is the test phase. In this phase, participants are required to accurately discern whether images appeared in the same position on the screen as during the encoding phase. Notably, 40 images maintain their original position, while the remaining images are presented in varying positions on the screen, ranging from close to more distant (four different distances, 20 pictures each). Participants indicate their responses by pressing a designated key for the same position and a different designated key for a different position.

#### Hospital anxiety and depression scale (HADS)

The HADS [39] serves as a comprehensive tool for assessing the participant’s level of anxiety and depressive symptomatology. This 14-item scale is divided into two subscales, with 7 items addressing anxiety-related symptoms, and the remaining 7 items focusing on symptoms associated with depression. Each item on the questionnaire is assigned a score, with six items scored positively on a scale ranging from 0 to 3, and eight items scored inversely from 3 to 0. Consequently, the total score for each subscale falls within the range of 0 to 21, providing a quantitative representation of anxiety and depression levels. Classification of participants is determined based on predefined cutoff points: “non-cases” (total score of 7 or less), “doubtful cases” (total score between 8 and 10), and “definite cases” (total score of 11 or higher). The established cutoff point of 8 out of 21 for anxiety or depression, as derived from the work of Bjelland and colleagues, adds consistency to the interpretation of results. The HADS has demonstrated good overall reliability, as well as good validity [40].

#### EuroQol quality of life (EQ-5D)

The EQ-5D [41] is an instrument that evaluates the quality of life, originating in the European context. It is a preference-based health-related quality-of-life measure with one question for each of the five dimensions including mobility, self-care, usual activities, pain/discomfort, and anxiety/depression. A weighted health index can be derived from this for an individual. In addition, participants will rate their general health status on a visual analogue scale ranging from 0 (worst general health status) to 100 (best general health status). The EQ-5D has shown good test–retest reliability, as well as good validity [42].

#### Quality of life in alzheimer’s disease (QoL-AD)

The Quality of Life in Alzheimer’s Disease (QoL-AD) developed by Logsdon [43] is a 13-item questionnaire tailored to evaluate changes in mood and physical and cognitive functioning, as well as the quality of relationships in the older adult population with probable AD. Participants are required to rate the 13 items according to their current status using a 4-point scale. Studies have shown that the QoL-AD has good to excellent reliability and validity [44–46].

#### Alzheimer’s disease cooperative study—activities of daily living (ADCS-ADL)

The ADCS-ADL [47] functions as an assessment tool for evaluating the competence of individuals diagnosed with AD across both basic and instrumental activities of daily living. This instrument can be administered in two formats: a caregiver-completed questionnaire format, or a structured interview conducted by a clinician or researcher in collaboration with a caregiver. Responses provided should pertain to the 4 weeks preceding the assessment. The basic activities of daily living [48] items each takes an ADL (e.g., eating) and provides descriptions of the level of competence, with the rater selecting the most appropriate option (e.g. ate without physical help and using a knife; used a fork or spoon but not a knife; used fingers to eat; was usually fed by someone else). The test–retest reliability of the ADCS-ADL is estimated to be high [48].

#### Neuropsychiatric inventory (NPI)

The NPI [49] provides a brief assessment of twelve distinct neuropsychiatric symptoms, including delusions, hallucinations, agitation/aggression, depression, anxiety, euphoria, apathy/indifference, disinhibition, irritability, aberrant motor behaviour, and sleeping problems and eating problems. A judicious screening question, ascertaining the presence or absence of behavioural changes, serves as the initial point of inquiry. Upon an affirmative response to the screening question, the frequency and severity ratings are determined. The frequency is rated on a 4-point Likert scale ranging from 1 (occasionally—less than once per week) to 4 (very frequently—daily or essentially continuously present). The severity is rated as 1 for mild—produces little distress in the patient, 2 for moderate—more disturbing to the patient but can be redirected by the caregiver and 3 for severe—very disturbing to the patient and difficult to redirect. The multiplication of frequency * severity results in a domain score. The total NPI score is calculated by the summation of the twelve domain scores. Inter-rater reliability ranged from 93.6 to 100 (depending on the sub-domain) and test–retest reliability is high [50].

### Plans to promote participant retention and complete follow-up {18b}

Completion of the study trial will result in the reimbursement of a total of 95 euros in vouchers for the participant and 50 euros in vouchers for the (informal) caregiver. In instances of premature termination of participation, the disbursement will be contingent on the number of test days attended by the participant. Provisions for travel-related expenditures will be separately reimbursed, encompassing a rate of 19 euro cents per kilometre and the full coverage of bus and train tickets (second class) adhering to established Dutch guidelines. Participants are called bi-weekly to monitor their well-being, address queries, and ensure ongoing engagement with the study.

In the event of an inability to collect primary outcome data, specifically the 15-VLT, either at baseline or the 6-month follow-up, resulting from circumstances such as discontinuation, the individual will be classified as a study dropout. It is noteworthy that the absence of other data or protocol deviations will not automatically lead to participant dropout. Any protocol deviations that arise will be meticulously recorded in the protocol/legislation deviation log for thorough documentation and subsequent analysis.

### Data management {19}

The data acquisition, entry, and management procedures will be exclusively conducted at Maastricht University. A total of 72 participants will be enrolled in the study, resulting in an approximate data volume of approximately 50 gigabytes. Maastricht University’s standard facilities will be employed for data storage and backup, involving the utilization of a secure server with daily data backups. Stringent adherence to the legal retention period, specifically a minimum of 25 years, and compliance with the General Data Protection Regulation (GDPR) will be observed throughout the data storage process. The study population compromises an elderly population with cognitive impairment, necessitating an extensive battery of tests and paper-and-pencil-based tests and questionnaires. A manual transfer of data from these papers to the eCRF in the CASTOR EDC database will be executed. Before entry into the eCRF, original data will undergo thorough accuracy checks. Instances of missing data will be categorized as measurement failed, not applicable, not asked, asked but unknown, and not performed. A comprehensive data management plan has been formulated by our data management team, consisting of an ICT developer and system administrator from our department, and a Project Specialist from the Clinical Trial Centre Maastricht (CTCM). Their collective expertise spans data management, monitoring, and pharmacovigilance. Adherence to regulatory frameworks, including the Quality Assurance for Research Involving Human Subjects Act, the Code of Conduct for Responsible Use of Human Tissue, and the Medical Treatment Contracts Act will be maintained. The eCRF in CASTOR incorporates built-in range checks for data values. To adhere to Good Clinical Practice (GCP), all modifications are systematically logged, and a justification for altering a field’s value is mandatory, courtesy of the audit feature. The eCRF in CASTOR offers a study progress overview which includes the participant record creation, visit completion, participant status, and visit status. Oversight of the eCRF building is appointed to our project quality specialist from the CTCM, who maintains a list of authorized individuals with editing privileges in CASTOR.

### Confidentiality {27}

To safeguard participant privacy, all collected data will undergo pseudonymization following GDPR guidelines. The code key will be securely managed by the principal investigator. Results will be coded to include the participant’s unique identification code (1 to 81) and the session (e.g. T0 for the first test day (baseline) and T4 for the last one). Printed questionnaires will be labelled with the unique identification code, session number, date, and time of measurement. Personal data, such as informed, consent will be coded (screening number), treated confidentially, and stored separately from other research data. Original data on paper will be stored in a locked cabinet within a secured office with restricted access in the department. Participants will be explicitly informed, through the informed consent process, about authorized individuals with access to their medical and personal data. This list includes the principal investigator, the Health and Youth Care Inspectorate (IGJ), and the study monitor (CTCM). Participants’ data will remain strictly confidential and will not be disclosed to unauthorized third parties, ensuring confidentially throughout the study.

### Plans for collection, laboratory evaluation and storage of biological specimens for molecular analysis in this trial and future use {33}

The storage of human biological material, specifically blood plasma and tear fluid samples, will adhere to a stringent scientific protocol set up with the Biobank of the MUMC + . The samples are securely stored and coded, each assigned a unique subject identification code, in the − 80 °C freezer situated in the ISO-certified Biobank of the MUMC + . The confidentiality of this code is safeguarded by the principal investigator. Upon exclusion from our clinical trial, participants meeting positive exclusion criteria during medical screening undergo immediate pre-analysis destruction of human biological material, such as blood plasma designated for biomarker and exosome collaborations. Participants are informed during the informed consent process that fully included the participant’s human biological material such as tear fluid and blood plasma samples for the collaboration studies, is retained post-conclusion of the ROMEMA study, preserving the potential for future research for a maximum of 5 years. For samples dispatched to external entities for analysis, specifically, blood plasma sent for roflumilast metabolite evaluation, will be pseudonymized. No identifiable participant information is transmitted to the external company. Post-analysis, the company is instructed to destroy the plasma samples. In the context of sub-studies and aforementioned collaborations, the sharing of data with other researchers exclusively involves pseudonymized information. Consistent protocols governing processing and storage timelines are uniformly applied across both the primary study and its associated sub-studies and collaborations.

### Statistical methods

#### Statistical methods for primary and secondary outcomes {20a}

Descriptive statistics for continuous parameters will include sample sizes, means and standard errors of the dependent variables, and covariates for each distinct level combination of factors. For categorical data, summary tables will present counts and percentages. Statistical summaries will be presented by treatment, sequence, or period. The repeated measures, namely the outcome variables of the cognitive assessments and the subjective well-being-related scales, will be analysed using mixed models. The between-subject factor will be the treatment group (three levels: placebo, 50 μg roflumilast, and 100 μg roflumilast). The scores of each task will be entered as the within-subject factor, as well as time (T1, i.e. acute, T2, i.e. 12 weeks, T3, i.e. 24 weeks, T4, i.e. 2-week follow-up). An additional interaction term between the treatment group and time is included to determine whether the different treatment groups will lead to different trajectories over time. Subject covariates included will be sex, age, and education. Additionally, at the end of the study, we will ask each participant which intervention arm they think they have received (placebo, 50 mcg roflumilast, or 100 mcg roflumilast). Because of exclusion and inclusion criteria related to the patient recruitment of the study, the population recruited will be homogenous. Note that groups will not be able to be matched because of the applied randomization block strategy. The significance level will be set at *a* = 0.05.

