### Outcomes {12}

#### Primary study parameter

The primary outcome measure is verbal memory using the 15-VLT [27]. The 15-VLT is chosen as our primary outcome because it assesses episodic memory—a cognitive domain linked with hippocampal function [18]. Considering the evidence of high PDE4 expression in the hippocampus [19] and observable atrophy in the medial temporal lobe regions of individuals diagnosed with MCI [17, 20]. Accordingly, a larger effect size for cognitive functions and tasks related to this brain area is expected. Variables include correct immediate recall on trial 1 to trial 5, correct total immediate recall (sum of all 5 trials), and correct delayed recall. Change from baseline to acute effects, change from baseline to 3 months, change from baseline to 6 months, and 6 months to follow-up will be statistically analysed.

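### As written, the mixed model gives baseline 15-VLT no place and names no term that isolates the 24-week dose-versus-placebo comparison

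*Protocol article*

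**What the plan says.** Section {20a} of the Protocol article sets out the model. On treatment: "The between-subject factor will be the treatment group (three levels: placebo" and the two doses. On time: "The scores of each task will be entered as the within-subject factor, as well as time (T1, i.e. acute", continuing through 12 weeks to "T3, i.e. 24 weeks, T4, i.e. 2-week follow-up". On adjustment: "Subject covariates included will be sex, age, and education". On the interaction: "An additional interaction term between the treatment group and time is included to determine whether the different treatment groups will lead to different trajectories". No term or contrast is named as the one that decides the primary hypotheses.

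Baseline is a collected session. Section {27} labels the sessions "T0 for the first test day (baseline) and T4 for the last one", and {18b} counts a participant without the baseline 15-VLT as a dropout.

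Section {12}, Primary study parameter, lists what will be analysed: "Change from baseline to acute effects, change from baseline to 3 months, change from baseline to 6 months, and 6 months to follow-up". Section {20a} does not say that the modelled score is a change.

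The two superiority hypotheses in {7} each compare one dose with placebo over 24 weeks of treatment.

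**The concern.** Three things do not fit together.

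- The outcomes section is built on change from baseline, while the model section has no baseline in it.
- The hypotheses concern week 24, which is T3. The model's two treatment terms are spread over T1 to T4: an acute visit, two visits during chronic treatment and one visit two weeks after the 24-week treatment period.
- The interaction is the only term with a stated inferential purpose. Without T0 it asks only whether arm differences vary among visits that all fall after dosing has begun.

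At stake is whether the primary result answers the stated question. In a trial of 24 evaluable participants per arm, precision from a baseline measure that is already collected would also go unused.

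A lesser matter is that {20a} lists the task score as a within-subject factor, although it is the response. The same section elsewhere calls the scores outcome variables, so this is loose wording.

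**Working it through.** **Inputs from the Protocol article.** d = 0.69, alpha 0.05 and 24 per group before dropout ({14}); three arms ({8}); four time levels ({20a}).

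**Assumptions.** Both doses have the same effect, SD is 1, data are complete, tests are two-sided without multiplicity adjustment, and visits are equally correlated at ρ = 0.5 to 0.8. The article gives no ρ.

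**The plan's own figure.** The step from 24 to 27 reproduces (24/0.9 = 26.7). The 24 does not follow from the stated inputs alone: a two-sided two-sample t-test with d = 0.69 and 80% power needs 34 per group. An F-test for repeated measures can give 24, but only with a correlation and a number of measurements that the article does not state. That is a separate matter. Here 24 is taken as given.

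**The two terms in the model.** Let c be the effect at each visit as a multiple of d, with mean c̄ over T1-T4. Placebo is 0 and both doses follow c. The common factor is (2/3)·n·d² = (2/3)·24·0.69² = 7.618.

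- Interaction: λ = 7.618·Σ(c − c̄)²/(1 − ρ), on 6 and 207 df.
- Treatment main effect: λ = 7.618·4c̄²/(1 + 3ρ), on 2 and 69 df.

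Numbers put in:

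- Constant effect: Σ(c − c̄)² = 0, so the interaction has λ = 0 and power equals alpha. Main effect λ = 30.47/2.5 = 12.19 at ρ = 0.5 and 30.47/3.4 = 8.96 at ρ = 0.8.
- Gone at T4: c̄ = 0.75 and Σ = 3·0.25² + 0.75² = 0.75. Interaction λ = 5.713/0.5 = 11.43 and 5.713/0.2 = 28.57. Main effect λ = 0.5625·12.19 = 6.86 and 0.5625·8.96 = 5.04.
- One visit only (T1 or T3): c̄ = 0.25 and Σ = 0.75² + 3·0.25² = 0.75, so the interaction λ is the same as when the effect is gone at T4. Main effect λ = 12.19/16 = 0.76 and 8.96/16 = 0.56.

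| Effect at T1, T2, T3, T4 | Interaction power, ρ 0.5 to 0.8 | Main-effect power, ρ 0.5 to 0.8 |
|---|---|---|
| 1, 1, 1, 1 | 5% throughout | 87% falling to 75% |
| 1, 1, 1, 0 | 70% rising to 99% | 63% falling to 49% |
| 1, 0, 0, 0 | 70% rising to 99% | 11% falling to 9% |
| 0, 0, 1, 0 | 70% rising to 99% | 11% falling to 9% |

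The interaction has the same power for an acute effect that has vanished by week 24 as for an effect sustained to week 24 and lost afterwards. The main effect has the same power for an effect at T1 only as for one at T3 only. Neither term speaks to T3 alone.

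**Week-24 pairwise comparison, 24 per arm, two-sided t-test.**

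- Raw score: standardised effect 0.69, power 65%.
- Change from baseline: 0.69/√(2(1 − ρ)) = 0.69, 0.77, 0.89 at ρ = 0.5, 0.6, 0.7; power 65%, 74%, 86%.
- Baseline as covariate: 0.69/√(1 − ρ²) = 0.80, 0.86, 0.97; power 77%, 83%, 91%. The residual variance falls by ρ², that is by 25%, 36% and 49%.

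**The case against.** A reader might infer that the planned analysis cannot detect an effect present at T1 and sustained to week 24, or that it rests on the interaction alone. The article supports neither reading.

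- The 5% figure needs the effect to stay at full size at T4, two weeks after the treatment period. If it holds to T3 and is gone at T4, the interaction has 70-99% power.
- Treatment group is in the model as a main effect, and that term has 75-87% power for a constant effect. The text introduces the interaction as additional and names no deciding test.
- Section {12} plans four changes and {20a} has four time levels, so the modelled scores may be meant as changes. On that reading baseline is not left out, and the remaining loss is change score against covariate adjustment.
- The protocol expects cumulative effects on top of the acute one, so a flat profile is only one possibility.
- Covariance structure and similar detail can sit in the full protocol or SAP.

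All of this stands as a limit on the claim, but it does not settle the point. The change-score reading has to be supplied by the reader, and the fourth change in {12} runs from 6 months, not from baseline. If all four were changes from T0, subtracting the same T0 from every visit would leave the T1-T4 interaction as it was, with 5% power for a constant effect. The main effect still averages the acute and post-treatment visits with week 24. How baseline enters, and which comparison decides, are things that {12} and {20a} state without agreeing.

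**Conclusion.** The point holds in this limited form. As written, {20a} gives baseline 15-VLT no place in the model, does not connect with the changes from baseline in {12}, and names two treatment terms, neither of which isolates the week-24 hypotheses of {7}. The analysis is not blind to a sustained effect. Its terms answer broader or different questions, with power that depends heavily on the time course.

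Adjusting for baseline and testing at T3 takes week-24 pairwise power from 65% on raw scores to 77%, 83% or 91% at ρ = 0.5, 0.6 or 0.7. Against change scores (65%, 74%, 86%) the gain is 12, 9 or 5 percentage points. All these figures rest on the assumptions listed with the calculation, above all on ρ. That the two terms do not isolate T3 does not depend on ρ.

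**What to change.** Reconcile {12} and {20a} on these lines:

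- The 15-VLT score is the dependent variable.
- Baseline enters either as a covariate with a baseline-by-time term, or as T0 in the response with a common baseline mean across arms.
- Treatment, categorical time, treatment by time, sex, age and education stay as fixed effects.
- The primary test is each dose versus placebo at T3 (24 weeks), estimated from this model.
- The T1, T2 and T4 contrasts and the overall interaction test are supportive.

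The cost is analysis wording only, because baseline 15-VLT is already collected. The wording should be settled before unblinded data are seen. Section {21b} plans an unblinded interim analysis once half of the participants have completed.

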### Objectives {7}

This study aims to examine whether a 24-week administration of roflumilast improves cognition in participants with (a)MCI and/or participants with mild AD dementia. The outcomes may provide a proof of concept on the potential of roflumilast as a pharmacotherapeutic treatment to enhance cognition, concurrently advancing our comprehension of the role played by PDE4 in human cognition. The primary objective is to validate the effect of roflumilast on episodic memory, assessed with the 15-word verbal learning test (15-VLT), in aMCI/mild AD dementia participants after chronic roflumilast treatment of 24 weeks (i.e. 6 months). Specifically, we expect an increase in correct recall of words on the immediate and delayed recall. The 15-VLT is particularly relevant, as it assesses episodic memory, a function primarily associated with the hippocampus [18]. Considering the evidence of high PDE4 expression in this specific brain structure [19] and observed (early) atrophy of the medial temporal lobe regions in (a)MCI/mild AD [17, 20], we expect a larger effect size for cognitive functions and tasks related to this brain area. Moreover, Hamel and colleagues have demonstrated the prognostic value of the 15-VLT performance decline, predicting dementia approximately 7 years preceding the formal diagnosis [21]. This temporal insight underscores the test’s relevance and its potential to serve as a sensitive indicator of cognitive trajectories in the context of (a)MCI and mild AD.

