### Eligibility criteria {10}

To be eligible to participate in this study, prospective participants must meet the following eligibility criteria: age within the range of 50 and 90 years, willingness and capability of both the participant and (informal) caregiver, to provide and sign informed consent. Additional criteria include a body mass index (BMI) between 18.5 and 35, an MMSE total score of 20 or higher, and a clinical diagnosis of aMCI or mild dementia (probable AD) diagnosis, which entails a memory performance on the delayed recall of the 15-VLT of one or more standard deviation(s) below the normative score, corrected for age, education, and sex. Furthermore, a global clinical dementia rating (CDR) scale total score of 0.5 or 1. Mild dementia (probable AD) is defined according to the Clinical Core Criteria of McKahn in 1987, updated in 2011 [23].

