### Methods for additional analyses (e.g. subgroup analyses) {20b}

Subgroups are defined based on baseline characteristics including sex, age, and education. We will investigate the effect of age in a stratified manner. By stratifying the groups into two age categories, e.g. < 70 and > 70, as well as stratifying the groups in two education categories, i.e. low and high education.

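### The plan calls the population homogeneous and leaves baseline diagnosis out of the model, although it enrols both aMCI and mild AD dementia; the cost is precision and chance imbalance, not systematic bias

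*Protocol article*

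**What the plan says.** All references are to the protocol article.

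- **Statistical methods {20a}** concludes from the inclusion and exclusion criteria that "the population recruited will be homogenous". The listed subject covariates are sex, age and education. The section adds that the block strategy means the groups cannot be matched.
- **Eligibility criteria {10}** require "a clinical diagnosis of aMCI or mild dementia (probable AD) diagnosis", "a global clinical dementia rating (CDR) scale total score of 0.5 or 1", "an MMSE total score of 20 or higher" and "age within the range of 50 and 90 years". Delayed recall on the 15-VLT must be at least one standard deviation below the norm.
- **Sequence generation {16a}** describes block randomisation in blocks of 12 and states no stratification factor.
- **Methods for additional analyses {20b}** names sex, age and education as subgroup variables. Diagnosis is not named.
- **Objectives {7}** opens with the question whether roflumilast "improves cognition in participants with (a)MCI and/or participants with mild AD dementia". The primary objective and the three primary hypotheses then treat the two diagnoses as one population.
- **Outcomes {12}** gives the primary variables as changes from baseline on the 15-VLT.

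**The concern.** The homogeneity sentence rests on the eligibility criteria, and those criteria do not support it. They admit two diagnostic stages that the article itself treats as distinct: the Background describes MCI as a possible transitional phase before dementia, and the Objectives plan to monitor conversion from (a)MCI to dementia, which only the aMCI participants can show.

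Disease stage is a plausible predictor of 15-VLT performance and of its course over 24 weeks. As described, nothing controls it. Allocation is not stratified by it, and the model does not adjust for it. Two things follow. By chance the arms may differ in their share of mild AD dementia, and outcome variation that a known baseline factor could explain stays in the residual. In a trial of 27 per arm, neither is negligible.

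**Working it through.** **Inputs from the article**

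- 27 randomised per arm, three arms, 1:1:1 (Trial design {8}, Sample size {14}).
- Planned effect d = 0.69 (Sample size {14}).
- No stratification factor stated (Sequence generation {16a}).

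**Inputs the article does not give, so assumed**

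- Share with mild AD dementia, p: 0.30 to 0.50.
- Difference between diagnoses on the 15-VLT, D, in within-diagnosis SD units: 0.5 to 1.5.

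The plan gives no figure on this point to reproduce. The argument does not depend on how its sample size was derived.

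**Step 1. The text.** Two admitted diagnoses, two CDR levels and an MMSE range of 20 to 30 are not one disease stage. The recall criterion caps memory performance but sets no floor. The homogeneity statement is therefore wrong as a description of who may enrol. The age range is a weaker argument, because age is already a covariate.

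**Step 2. How often the arms differ in diagnosis.** Treat the arms as independent.

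SD of the difference in AD share between two arms = √(2p(1−p)/27).

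- p = 0.50: √(0.50/27) = 0.136
- p = 0.30: √(0.42/27) = 0.125

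With 27 per arm, the smallest gap of at least 20 points is 6 participants (6/27 = 22.2 points). Exact binomial probabilities of such a gap:

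| AD share | A given pair of arms | Some pair among the three |
|---|---|---|
| 0.30 | 10.1% | 23% |
| 0.50 | 13.4% | 29% |

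The expected absolute gap for a given pair is about 10 points at p = 0.30 and 11 points at p = 0.50. A 20-point gap is thus a tail case, but not a rare one.

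**Step 3. What a 20-point gap would do to raw scores.**

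Shift in an unadjusted contrast = 0.20 × D.

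- D = 0.5: 0.10 SD
- D = 1.0: 0.20 SD
- D = 1.5: 0.30 SD

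The planned effect is 0.69.

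**Step 4. Precision on raw scores.**

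Share of outcome variance explained by diagnosis = p(1−p)D² / (1 + p(1−p)D²). At p = 0.50:

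- D = 0.5: 0.0625/1.0625 = 6%
- D = 1.0: 0.25/1.25 = 20%
- D = 1.5: 0.5625/1.5625 = 36%

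**Step 5. Why Steps 3 and 4 are upper illustrations.** The primary variables are changes from baseline. A stable difference in level between the diagnoses largely cancels in a change score. What remains is any difference in mean 24-week change. If that difference is δ, a 20-point gap shifts the contrast by 0.20 × δ. The article gives nothing from which to set δ, so the size for the planned variable cannot be stated beyond being smaller than the raw-score figures suggest.

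**Step 6. What a look by diagnosis could show.** If one diagnosis contributes 8 to 16 participants per arm, a two-sided t-test at 0.05 with d = 0.69 has power of 0.25 to 0.47. An estimate by diagnosis can describe, but it cannot settle the matter.

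**The case against.** The strongest reply is that the pooled analysis matches the formal question. The primary objective and all three hypotheses combine aMCI and mild AD dementia. A reader might infer from "improves cognition in participants with (a)MCI and/or participants with mild AD dementia" that the trial undertakes to answer for each diagnosis separately. That introductory phrase does not carry so much weight, and the absence of a diagnosis-specific test does not contradict the objectives.

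It can also be said that randomisation deals with imbalance. A reader might take the 0.10 to 0.30 SD shift as a bias of the design. It is not: the contrast is unbiased on average, and its standard error already allows for chance imbalance. The argument for adjustment is precision and a result less dependent on the particular allocation. The shift also applies to raw scores under assumed inputs.

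Third, the sample is narrower than the two labels suggest. The recall criterion and a long exclusion list remove many other sources of impairment. They do not reduce the sample to one stage.

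Fourth, the subgroup list is introduced as including the three variables, so it is not strictly closed, and an extra exploratory subgroup may sit in an analysis plan that is not shown. That stands, so the missing subgroup is not a fault in itself. The covariate list is different: the article fixes it and sets beside it a reason that its own criteria refute.

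Finally, "By stratifying the groups into two age categories, e.g. < 70 and > 70" leaves out anyone aged exactly 70, and a reader might count that as a further defect. The split is given only as an example and has nothing to do with diagnosis, so it adds nothing to this point.

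**Conclusion.** The point holds in a limited form. The homogeneity sentence is inaccurate on the article's own eligibility criteria, and the stated model leaves out a baseline factor that divides the sample into two disease stages and on which no stratification is stated. The consequence is lost precision and exposure to chance imbalance: about a 10 to 13% chance of a gap of 20 points or more between two given arms, assuming 30 to 50% with AD dementia.

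How far this moves the 15-VLT contrast cannot be fixed from the article. The raw-score figures are ceilings that rest on an assumed difference of 0.5 to 1.5 SD, and analysing change from baseline lowers them. The article does not support a claim of systematic bias, or that the pooled analysis fails the stated hypotheses. The change is worth making because it is specific and nearly free.

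**What to change.** 1. Delete the sentence in Statistical methods {20a} that calls the population homogeneous.
2. Before unblinding, add baseline diagnosis (aMCI versus mild AD dementia, as recorded at screening) as a fixed covariate in the primary mixed model, together with the baseline 15-VLT score. Use the diagnosis itself and do not leave CDR 0.5 versus 1 as an alternative, because the eligibility section does not equate the two.
3. Optionally, report the treatment-by-diagnosis estimate at 24 weeks with confidence intervals, labelled exploratory and low-powered. Make no confirmatory claim for either diagnosis.

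Cost: one model degree of freedom for diagnosis, one more for the baseline score, and a short change of wording. Diagnosis is confirmed at the screening visit and the 15-VLT is already measured at baseline, so no new data are needed. Because recruitment had already started, stratifying the randomisation could help only later participants; the covariate covers everyone.
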